## Abstract

**Background:**

Dysphagia occurs in up to 50% of patients admitted to hospital with acute strokes with up to 27% remaining by seven days. Up to 8% continue to have swallowing problems six months after their stroke with 1.7% still requiring enteral feeding. Nasogastric tubes (NGT) are the most commonly used method for providing enteral nutrition in early stroke, however they are easily and frequently removed leading to inadequate nutrition, early PEG (Percutaneous Endoscopic Gastrostomy) insertion or abandoning of feeding attempts. Looped nasogastric tube feeding may improve the delivery of nutrition to such patients.

**Methods:**

Three centre, two arm randomised controlled trial, with 50 participants in each arm comparing loop (the intervention) versus conventional nasogastric tube feeding. The primary outcome measure is proportion of intended feed delivered in the first 2 weeks. The study is designed to show a mean increase of feed delivery of 16% in the intervention group as compared with the control group, with 90% power at a 5% significance level. Secondary outcomes are treatment failures, mean volume of feed received, adverse events, cost-effectiveness, number of chest x-rays, number of nasogastric tubes and tolerability.

**Trial Registration:**

ISRCTN Number: ISRCTN61174381

## Background

Dysphagia occurs in up to 50% of patients admitted to hospital with hemispheric stroke [1-4]; up to 27% remain at risk of aspiration by seven days, and up to 8% have swallowing problems six months after their stroke [5] with 1.7% still requiring tube feeding [6]. Nutritional supplementation can reduce mortality in older people at risk of malnutrition, although this has not been shown specifically in the context of stroke [7]. During the period when patients with stroke are unable to take their full dietary requirements normally, the delivery of a liquid feed through a fine bore nasogastric tube is commonly used. The tube is usually secured with adhesive tape around the tube and to the patients face, and is often hooked behind the ear, where more adhesive tape may be used.

Unfortunately nasogastric tubes are frequently inadvertently dislodged, due to confusion, restlessness, communication and attention disorders during handling or normal movement. Partial dislodgement may leave the tube misplaced in the lungs, leading to a risk of aspiration. Dislodgement means that the tube needs to be re-sited, possibly causing distress and discomfort to the patient. Re-siting takes up nursing staff time, and may require a chest x-ray to confirm that the tip of the tube is in the stomach (especially in light of recent guidance [8]), adding further costs and inconvenience. With multiple re-sitings, and the associated delays, the amount of food that is delivered by conventional nasogastric tube may be significantly below the intended amount [9,10]. This gives rise to a risk of malnutrition, which is associated with poor outcomes [11-13]. In view of these difficulties, percutaneous endoscopic gastrostomies are considered but the results from the FOOD trial suggest that early PEG feeding may be injurious [14]. It would be helpful to find a simple and feasible means of using nasogastric tube feeding in acutely dysphagic stroke patients that reduces the likelihood of inadvertent nasogastric tube dislodgment.

Looped nasogastric feeding is a novel technique, early reports of which suggest that it allows more secure placement of a NG tube, but which is completely and easily reversible [15]. In this technique, the end result is that a loop is secured around the nasal septum; this loop is used to secure the nasogastric tube in place. This technique may result in considerably less tube dislodgement and more reliable feeding without compromising patient acceptability.

## Methods/Design

### Study design and participants

#### Study design

Three centre, two arm randomised controlled trial (Queens Medical Centre, Nottingham; Nottingham City Hospital, Derbyshire Royal Infirmary).

#### Subject definition

Any adult (> 18 years of age) with an acute clinically diagnosed stroke as defined by WHO standards ('A focal or at times global neurological impairment of sudden onset and lasting more than 24 hours, (or leading to death) and of presumed vascular origin') [16]; managed on the Stroke Unit. A clinical decision to attempt nasogastric tube feeding according to usual protocols has been made by the attending clinical team.

#### Exclusion criteria

Those not consenting to either NGT placement or to entry into the trial. Those for whom NG feeding is determined not to be in their best interests. Pregnant women. Those with contraindications to NG feeding (nasal trauma/malignancies).

#### Interventions

The research fellow and specialist stroke nurses will be trained in siting the looped nasogastric tube (LNGT) as well as conventional nasogastric tubes and will in turn train the ward based nurses in the same techniques.

#### Product details

The nasal loop is manufactured by Applied Medical Technology Inc (United States) and distributed in the UK by Pro-Care Ltd (UK). The CE mark is 93/42/EEC and the product has been through the FDA approval process in the United States.

#### Intervention group

The intervention group will receive all usual care except that the looped nasogastric feeding tube will be used for feed delivery. Subjects will have the loop component of the NGT sited as per manufacturer's instructions. The loop will be sited by either the research fellow, stroke nurses or ward staff who will have been fully trained in placing the loop. A nasogastric tube (NGT) will be passed and once in place fixed using the loop, thus creating the looped nasogastric tube. Upon confirmation that the NGT is correctly located, feeding will be commenced on an incremental fashion as per local protocols, which will vary between the centres

#### Control group

Participants will have a conventional nasogastric tube (CNGT) sited either by trained ward staff or by the study nurse. Upon confirmation that the NGT is correctly located, feeding will be commenced on an incremental fashion as per local protocols.

### Hypotheses

This trial will assess feed and fluid delivery by nasogastric tube; it does not seek primarily to assess nutritional outcomes, functional improvement or mortality. There are no well validated techniques for measuring change in nutritional outcomes, especially in the context of stroke. Anthropometric measures are difficult to obtain, because of immobility and inability to stand and so measure height. Biochemical indices (albumin, haemoglobin) are liable to confounding because of intercurrent infection and frequent comorbidity. Weight at baseline and two weeks will be measured and where possible demispan, allowing calculation of the Demiquet index [17] in order to provide a measure of nutritional status. It is unlikely that this trial will be able to show an improvement in function or nutrition, as the power requirements would require a number of participants an order of magnitude greater than anticipated; similar arguments can be applied to mortality.

The outcome measures are confined to the first two weeks following the onset of stroke, as after two weeks, there is the risk of contamination as individuals are offered PEG tubes as part of usual practice. For the purposes of this trial, PEG use within two weeks is considered as a failure of nasogastric feeding.

#### Primary hypothesis

Does use of the looped nasogastric tube in dysphagic acute stroke patients result in a greater proportion of nutritional prescription received per patient over a two week period than conventional nasogastric tube use?

#### Secondary hypotheses

Does use of the looped nasogastric tube in dysphagic acute stroke patients reduce the number of treatment failures during nasogastric feeding?

Does the use of the looped nasogastric tube enable greater total delivery of artificial nutrition?

What is the frequency of adverse events using this technique?

Is the looped nasogastric tube cost-effective compared to conventional nasogastric feeding, from an NHS perspective?

Does this technique reduce the proportion of patients requiring early PEG insertions?

Does looped nasogastric feeding improve nutritional indices compared to conventional nasogastric feeding?

Is loop feeding acceptable to patients?

### Sample size

Pilot information shows that conventional nasogastric feeding delivers approximately 43.5% of intended food (n = 4) [18] though based on small numbers, this audit data is consistent with previously published figures for NG feed delivery [10]. We estimate that an improvement to less than 60% would not be clinically worthwhile. No previous studies have been performed to assess the percentage of intended food that is delivered by a looped nasogastric tube in a comparable population. Therefore, we have assumed a conservative estimate for the common standard deviation, which relates to an effect size of 0.660.

A sample size of 50 in each group will have 90% power to be able to detect a 16.5% difference in the proportion of intended feed delivered between the conventional and looped nasogastric tube groups within two weeks assuming that the common standard deviation is 25%^1 ^using an independent two sample t test with a 5% two-sided significance level. Allowing for dropouts (10%), we aim to recruit a total sample size of 110 patients.

### Randomisation and blinding

Participants will be randomised with equal probability to usual care or the looped nasogastric technique by a computer generated pseudo-random list using random permuted blocks of randomly varying size, created by the Nottingham Clinical Trials Support Unit (CTSU) in accordance with their standard operating procedures and held on a secure server. The randomisation will be stratified by centre and Oxford stroke classification (TACS versus non-TACS). TACS describes the most severe form of stroke, with 90% of survivors either dead or heavily dependent at one year. The outcome for individuals with a non-TACS stroke is more favourable.

Access to the sequence will be confined to the CTSU Data Manager. Investigators will access the treatment allocation for each subject by means of a remote, internet-based randomisation system developed and maintained by the Nottingham CTSU. The sequence of treatment allocations will be concealed until interventions have all been assigned and recruitment, data collection, and statistical analyses are complete.

It will not be possible to blind participants nor the data collectors to the treatment allocation, due to the nature of the intervention. However, all outcomes will be assessed by a blinded assessor and analysis will be blind to the treatment allocation.

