#### Primary outcome

The volume of feed and fluid administered via the NGT will be recorded by ward nursing staff on a daily basis. The amount of feed delivered can be accurately recorded as feed delivery is regulated using digital pumps. The pumps enable accurate recording of the amount of feed delivered (or not delivered) in millilitres. This information will be collated by the Research Fellow when they visit the stroke unit each day.

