#### Secondary outcomes

Tube usage and tube related complications will be monitored and the data collated using, to be completed for each patient every 24 hours. The form will be completed by ward staff with the support of the research fellow.

Treatment failure/completed treatment (where treatment failure means any occasion where attempts at nasogastric tube feeding is ceased before normal oral intake is established, and includes multiple failed attempts at passing a tube, use of a PEG (in the first two weeks), death or deterioration such that feeding is considered unsafe or unwanted) will also be recorded on this form. In such cases, the circumstances will be abstracted from the medical notes (< 1/2 side A4), without reference to treatment group. The abstract will then be anonymised and e-mailed to a medically qualified blinded assessor (RH). The assessor will then assign the outcome as failure/no failure (e.g. when feeding stopped because of return of oral feeding).

Weight (kilograms) and demispan (in cm: using stainless steel tape measure, finger roots to sternal notch), will be measured at baseline and at two weeks.

Both groups will be asked to complete a tolerability questionnaire regarding NG feeding, this will be adapted for dysphasic patients.

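### The protocol says all outcomes are assessed blind, but it describes a blinded assessor only for treatment failure and aspiration pneumonia, and none for the primary outcome

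*Protocol article*

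**What the plan says.** Under Randomisation and blinding, the protocol article first concedes that "It will not be possible to blind participants nor the data collectors to the treatment allocation, due to the nature of the intervention". It then says that, even so, "all outcomes will be assessed by a blinded assessor and analysis will be blind to the treatment allocation".

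The sections under Ascertainment of outcomes describe the actual procedures. For the primary outcome, "The volume of feed and fluid administered via the NGT will be recorded by ward nursing staff on a daily basis", and then "This information will be collated by the Research Fellow when they visit the stroke unit each day". Feed delivery is said to be regulated by digital pumps that give accurate volumes. For tube usage and tube-related complications, "The form will be completed by ward staff with the support of the research fellow". Treatment failure follows a different route: the circumstances are abstracted from the notes without reference to group, anonymised, and sent to a medically qualified blinded assessor. Aspiration pneumonia also goes to a blinded assessor as a case-note abstract.

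Under Intervention group, "The loop will be sited by either the research fellow, stroke nurses or ward staff". The people who record and collate the primary outcome are thus among those who may place the device.

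**The concern.** The blinding statement is a positive claim about a design property, and it covers every outcome, including the one that decides the trial. If the procedures do not deliver it, anyone judging the risk of detection bias from that sentence may credit the primary outcome with a protection that the protocol never describes.

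This is not a detail that a condensed article may leave to the full protocol. The article makes the claim itself, then sets out ascertainment outcome by outcome. Where a blinded step exists, it spells the step out. The primary outcome has its own ascertainment section, and no such step appears there.

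**Working it through.** No figure bears on this point, so the check compares text with text. Each outcome listed under Outcome measurements, Adverse events and Follow up measures is matched to the person whom the ascertainment sections (or, for tolerability, the list of secondary outcomes) name as recording or judging it.

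| Outcome | Who records or rates it | Blinded assessor described? |
|---|---|---|
| Percentage of prescription received (primary) | Ward nurses; collated by the research fellow | No |
| Tube usage, re-siting, tube complications | Ward staff, supported by the research fellow | No |
| Treatment failure | Ward form, then anonymised abstract of the notes | **Yes** |
| Early PEG as a separate outcome | None named | Only in part: PEG within two weeks is a component of treatment failure |
| Weight and demispan | None named | No |
| Tolerability | Patients, relatives and nurses | No |
| Nasal irritation, bleeding, discomfort | Ward nurses and the clinical fellow | No |
| Diarrhoea | Ward stool charts | No |
| Aspiration pneumonia | Case-note abstract | **Yes** |
| Gastrointestinal bleeding, refeeding syndrome | None named | No |
| Three-month measures | Research fellow (records, GP) and postal questionnaire | No |

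Result: two outcomes have a blinded assessor, against a claim of all.

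Two steps then decide whether the claim can be rescued.

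1. *Tolerability.* The rater is the participant, a relative or a nurse. The protocol says participants cannot be blinded. For the participants' own ratings, blind assessment is impossible, so the claim about all outcomes fails on this item alone.
2. *Primary outcome.* After collation by the research fellow, no further assessment is described. The blind analysis is a separate promise in the same sentence and cannot also serve as the blind assessment.

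How exposed is the primary outcome? It has three parts, set out under Definition of primary outcome and in the ascertainment section:

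- *Feed volume.* Regulated by pump and read in millilitres. This leaves little room for biased recording, although ward nurses still enter the figures.
- *Fluid volume.* The outcome counts all feed and fluids, but the protocol claims pump accuracy for feed only. Fluids rest on what the ward charts.
- *End of the window.* It closes at two weeks, or sooner if the clinical team ends nasogastric feeding. That is a judgement by staff who can see the device. The blinded assessor's stated task is to classify failure or no failure, not to set this date.

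**The case against.** The best defence is that collecting and assessing are different acts. The protocol admits, in the sentence before the claim, that data collectors are unblinded, and it promises blinding only for assessment and analysis. Nurses recording volumes and a research fellow collating them are collection. This stands as far as it goes: the protocol does not hide open-label collection, and a reader who takes both sentences together is warned. It does not rescue the claim, because no assessment step for the primary outcome follows, and self-rated tolerability leaves no room for one.

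The second defence is that pump readings are objective, so blinding matters little here. For feed volume this is a real mitigation. It covers neither charted fluids nor the stopping point, and it does not make the sentence true.

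Stronger readings are tempting but unsupported:

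- *That no blinded handling of the primary outcome exists.* The article is condensed, and the percentage might be calculated from coded data. The text shows only that no blinded step is described.
- *That the primary result will be biased.* The document gives nothing from which a direction or size could be derived.
- *That every other outcome is recorded unblinded.* For weight, demispan, gastrointestinal bleeding and refeeding syndrome no recorder is named, so this cannot be asserted.

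**Conclusion.** The point holds as an internal contradiction. The protocol's statement that all outcomes are assessed blind is wrong as written: its own procedures describe blinded assessment for treatment failure and aspiration pneumonia, with partial cover for early PEG through the failure definition, and for nothing else. The primary outcome is among those without a described blinded step, which is why the sentence needs correcting.

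The conclusion rests on reading the ascertainment sections as a fair account of who does what. If the full protocol contains a masked step for the primary outcome, the fault narrows to tolerability and the other outcomes without one, and the article should say what that step is. The sample size and planned comparison are unaffected. Open-label collection is unavoidable with this device and is not itself a fault.

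**What to change.** *Wording.* Limit the claim: treatment failure and aspiration pneumonia are adjudicated blind and the analysis is blind; the primary outcome and the remaining ward-recorded and self-reported outcomes are collected open-label. Say who measures weight and demispan and who records gastrointestinal bleeding and refeeding syndrome, rather than labelling these either way by default.

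*Masked calculation.* Have delivered over intended calculated under coded allocation from three sources: daily pump feed volumes, charted fluid volumes and the dated dietician prescriptions. Two conditions matter. Pump totals alone will not do, because the outcome includes fluids and using feed only could change the endpoint. The person calculating must have no access to the allocation sequence, which excludes the CTSU Data Manager, to whom the protocol gives that access.

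*Cost.* The blinding statement becomes less favourable, and there is a small amount of extra data handling. Recruitment began in September 2006, so the masked calculation should be documented as a change made during the trial if it is not already in place. It does not blind the decision to end feeding, so the open-label disclosure is needed either way.

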### Procedures and observations

#### Consent

Verbal and/or written consent will be obtained from all participants where possible. Where dysphasia or other barriers exist to obtaining verbal consent, if the clinicians affirm that it is in the patient's best interest to participate (at risk of minimal harm from the intervention), assent will be sought from the next of kin, mirroring clinical practice where consent to nasogastric feeding is established. Information sheets will be provided to participants and family members. Individuals who are entered into the trial through a process of assent, will be reviewed regularly and given the opportunity for fully informed consent. They may choose to withdraw from the study at any stage without compromising their care. Consent processes are based on Department of Health and MRC Guidance [19].

### Patients not recruited into the study

Patients not recruited into the study will receive all usual care, but will not be eligible for the looped nasogastric tube, which is not standard therapy.

### Baseline measurements

Age, sex, hospital, previous stroke, residential status, Oxford stroke classification, NIHSS (National Institute of Health Stroke Scale), time from stroke onset, Glasgow Coma Scale score at 24 hours, weight and demi-span, and whether treated for chest infection between admission and allocation.

### Outcome measurements

#### Definition of primary outcome

Primary outcome: percentage of nutritional prescription received (amount delivered/amount intended as per dietician's prescription, including all feed and fluids) delivered in the two weeks from allocation or at the point NG feeding is stopped earlier on clinical grounds.

#### Secondary outcomes

• Number of times tube re-sited in two weeks; treatment failure/completed treatment as specified (where treatment failure means any occasion where attempts at nasogastric tube feeding is ceased before normal oral intake is established, and includes multiple failed attempts at passing a tube, use of a PEG (in first two weeks), death or deterioration such that feeding is considered unsafe or unwanted)

• Mean volume of nasogastric feed delivered in the two weeks from allocation

• Proportion of patients requiring early PEG insertions

• The technical efficiency (that is whether the best outcome is being achieved within a given set of resources) of looped nasogastric feeding after stroke compared to ordinary nasogastric tubes will be assessed from an NHS perspective to see if this new technology offers value for money. An intervention specific outcome will be used to estimate an incremental cost-effectiveness ratio in the form of a cost per change in percentage nutritional prescription received.

• Change in Demiquet index from baseline to two weeks (weight in kilograms)

• Tolerability/acceptability of technique by questionnaires to patients, families and nursing staff.

### Adverse events

Tube related: reports of nasal irritation, complications associated with nasogastric tube use

Aspiration pneumonia

Diarrhoea

Gastrointestinal bleeding

Refeeding syndrome

